**Figure 1 F1:**
[figure not shown]
Maps of the study areas for the proposed work in Sidama, Ethiopia.

### Sample size calculations

Using the 2016 Ethiopia Demographic Health Survey^22^ and focusing on our primary anthropometric outcome variable, we have mean height-for-age z-scores (HAZ) in children under the age of 36 months of −1.46 (SD=1.56). With the significance level set at 5%, power at 80%, allowing for 10% attrition between survey rounds, and accounting for that not all children consume milk, the study requires approximately 1000 children to detect a 0.3 SD improvement in child HAZ. This minimum detectable effect size corresponds to the estimated association between household cow ownership and child HAZ (children starting at 6–18 months of age) in a study by Hoddinott *et al* in rural Ethiopia.^23^ Since we focus directly on children’s dairy consumption rather than cattle ownership, and our exposure variable is continuous rather than dichotomous, the expected magnitude of the association is likely to be larger than the association documented in Hoddinott *et al*.^23^ Thus, we expect this sample size to offer sufficient precision to detect positive and/or negative associations between AFM1 exposure and growth outcomes in this population.

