### Study design and data collection

The target group of the main study is 1000 caregivers and their children aged 6–18 months from urban or peri-urban households that raise dairy cattle. In the initial visit, a baseline survey will be used to collect data such as anthropometric measurements, child’s diet and socio-demographic factors among other data. After the baseline survey, short phone-based interviews will be carried out every 6 months to assess the variability in the child’s milk consumption and dairy production factors. Our end-line visit, mainly to collect data on child’s anthropometric measurements, will be carried out 18 months after the initial visit. **Patient and public involvement**: the interview results from the formative research described above on public participants in Sidama, Ethiopia, aided the selection of households in the second part of our work.

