### Study setting

The study will be conducted in two districts, Wondo Genet and Hawassa Zuria of Sidama region in Ethiopia (figure 1). These districts are purposely selected due to the common practice of using cow’s milk as complementary food for young children, availability of commercial milk, potential for AFB_1_ contamination in livestock feeds and variation in market access to feed.

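### The claim of sufficient precision for AFM1 does not follow from the sample-size calculation, and the figure of 1000 cannot be verified because the unit of the 0.3 effect and the assumed milk share are not clear

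*Protocol article*

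**What the plan says.** The Protocol article, Sample size calculations, takes a mean HAZ of −1.46 (SD 1.56) from a national survey. With 5% significance, 80% power, 10% attrition between rounds and an allowance for children who do not drink milk, it states that "the study requires approximately 1000 children to detect a 0.3 SD improvement in child HAZ". The 0.3 is said to match the association between household cow ownership and HAZ in a cited study from rural Ethiopia.

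The section then argues that the present association should exceed that benchmark. It gives two reasons: the study looks directly at dairy consumption, and "our exposure variable is continuous rather than dichotomous, the expected magnitude of the association is likely to be larger". From this it concludes: "Thus, we expect this sample size to offer sufficient precision to detect positive and/or negative associations between AFM1 exposure and growth outcomes".

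Other sections describe what will be estimated:

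- Study design and data collection draws participants "from urban or peri-urban households that raise dairy cattle".
- Study setting says the districts were chosen partly for the "common practice of using cow’s milk as complementary food for young children".
- The second item under Objectives limits the AFM1 question to children who consume milk.
- Equation (2) under Data analysis estimates the AFM1 coefficient (beta_A) adjusted for milk intake, milk nutrients and pathogens, maize consumption and the other covariates.

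**The concern.** The AFM1 sentence is an inference, and its premises concern something else. The only calculation is for an effect benchmarked on cow ownership, which does not vary in a cohort where every household keeps dairy cattle. The step from that effect to a larger one rests partly on the exposure being continuous. Continuity can improve efficiency, but it does not enlarge an association, because a slope depends on the unit of the exposure. Error in a one-day recall, which the Control variables section itself acknowledges, would tend to shrink the slope.

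The figure of 1000 raises a second problem. HAZ is already a z-score, so 0.3 SD can mean 0.3 HAZ points or 0.3 times the quoted SD of 1.56. The required number depends heavily on which is meant and on the share of milk drinkers, which is not given.

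AFM1 is the study's central question, and the Discussion says that a finding of little or no growth harm could support less stringent milk standards. Readers of a null beta_A need to know how large a harm the study could have missed.

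**Working it through.** **Inputs from Sample size calculations:** alpha 5%, power 80%, SD 1.56, attrition 10%, effect 0.3. **Assumed, because not stated:** two-sided test, normal approximation, comparison of milk drinkers (share p) with non-drinkers, and 10% attrition applied once, so 900 of 1000 are analysed.

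**Formula.** (1.960 + 0.842)² = 7.849. The number analysed is N = 7.849 / (d² × p(1−p)), and the number enrolled is N / 0.9.

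**Reading A, 0.3 of the survey SD.** d = 0.3, that is 0.3 × 1.56 = 0.47 HAZ points.

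- p = 0.50: 7.849 / (0.09 × 0.25) = 349 analysed, 388 enrolled.
- p = 0.89: 7.849 / (0.09 × 0.0979) = 891 analysed, 990 enrolled.

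**Reading B, 0.3 HAZ points.** d = 0.3 / 1.56 = 0.1923, d² = 0.0370.

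- p = 0.50: 849 analysed, 943 enrolled.
- p = 0.60: 885 analysed, 983 enrolled.
- p = 0.80: 1327 analysed, 1474 enrolled.

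The plan's figure of about 1000 can therefore be reached under either reading, but at quite different milk shares.

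**What the ambiguity means for power.** Power = Φ(d × √(N p(1−p)) − 1.96). With N = 900 and p = 0.89, √(900 × 0.0979) = 9.39.

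- Reading A: Φ(0.3 × 9.39 − 1.96) = Φ(0.86), about 80%.
- Reading B: Φ(0.1923 × 9.39 − 1.96) = Φ(−0.15), about 44%.

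**AFM1 coefficient.** The article gives no inputs, so this is an illustration. Assume that 50% to 80% of 900 completers drink milk, that is 450 to 720 children, and that the residual SD is 1.56. The minimum detectable slope per SD of exposure is 1.56 × 2.802 / √(n(1−R²)), where R² is the share of the variance of exposure explained by the covariates.

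| Consumers | R² = 0 | R² = 0.5 |
|---|---|---|
| 450 | 0.21 HAZ | 0.29 HAZ |
| 720 | 0.16 HAZ | 0.23 HAZ |

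Both columns take exposure as measured without error. With classical error, the detectable slope on the true exposure is divided by the square root of the reliability, so it is larger.

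**The case against.** The strongest reply is that the 1000 is not shown to be wrong, and that stands. A reader might infer that 0.3 SD needs only about 390 children and that the figure fails to reproduce. But 390 assumes a 50:50 split, while the same sentence says that non-drinkers were allowed for. A high milk share is plausible in cattle-owning households in these districts, and 89% drinkers gives 990. The full protocol may state the share.

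Other stronger readings also go beyond the document:

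- **A slip between SD and HAZ points.** This is possible but unproven. Outcome variables uses SD for z-score units when it defines stunting, and either reading can reach about 1000.
- **Loss of 10% in each of three six-month intervals**, leaving 1000 × 0.9³ = 729. HAZ is measured only at baseline and end line. The contacts between are phone interviews, and a missed call does not lose the end-line measurement.
- **Power by drinker share as a property of the planned analysis.** The model uses milk intake as a continuous regressor, so its power depends on the spread of intake. Covariate adjustment may also lower the residual SD. The 80% and 44% show only what the ambiguity is worth in a two-group comparison.
- **The study is too small for AFM1.** Under ideal assumptions the detectable slope is modest, and the less favourable values rest on an assumed R². The document does not show inadequate precision.

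The authors can also fairly say that ownership is only a benchmark, that direct measurement of consumption was their first reason for expecting a larger association, and that repeat recalls and phone surveys reduce measurement error. None of this supplies a basis for the AFM1 sentence or rescues the argument from continuity.

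**Conclusion.** The point holds as one of unsupported inference and unverifiable arithmetic. The article claims adequate precision for its main question from a calculation that does not bear on beta_A, and one of its bridging arguments is wrong in principle. That conclusion needs no numerical assumption.

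The 1000 is ambiguous. Depending on unit and milk share, the same stated inputs give anything from about 388 to 1474 enrolled over the splits shown. These figures rest on a two-sided, two-group normal approximation with 10% attrition applied once.

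For AFM1, 0.16 to 0.29 HAZ per SD of exposure is illustrative. It depends on assumed consumer numbers and R² and would be larger with exposure error. Whether that precision is sufficient is for the authors to argue once the figure is stated.

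**What to change.** Keep N = 1000 and rewrite the paragraph:

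1. Say whether 0.3 means 0.3 of the survey SD or 0.3 HAZ points. Restate the detectable effect in that unit, with the test's sidedness, the assumed milk share and the total attrition to end line. A slope per SD of milk intake would match the planned model best.
2. Delete the argument that a continuous exposure implies a larger association.
3. Replace the concluding AFM1 sentence with a minimum detectable beta_A per SD of AFM1 exposure among milk consumers, over stated ranges of consumer number, correlation with the covariates and exposure reliability.

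The cost is one paragraph and no additional children. The downside is that the stated precision will look less favourable than it does now.

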### Sampling procedures

Our formative research found that feed ingredients and type varied by herd size and season. Based on these findings, we will classify the dairy cow-owning households into small herd size (one to three cattle) and large herd size (four or more cattle) and randomly select a total of 500 households each from both groups. The two study districts have a list of herd sizes to provide the sampling frame. Within these two groups, all households have an equal chance of being selected.

### Outcome variables

Anthropometric status indicators are the main outcome variables for this study. Anthropometric measurements—weight, height/length, mid-upper arm circumference (MUAC) and head circumference—will be collected from the children at baseline and end line. Height/length will be measured using height/length boards, with the measurements recorded to the nearest 0.1 cm. Weight will be measured using a digital weighing scale (Seca 874 digital floor scale) and recorded to the nearest 0.1 kg. Head circumference will be measured by using a Seca paediatric head circumference measuring band to the nearest 0.1 cm decimal.

Using the WHO 2006 child growth standards, we will calculate HAZ, weight-for-height z-scores (WLZ), weight-for-age z-scores (WAZ) and head circumference-for-age z-scores (HCZ). The HAZ is the primary variable of interest and as secondary outcomes, we will consider the dichotomous variable of stunting (ie, HAZ below −2 SD), WLZ and wasting (ie, WLZ below −2 SD), WAZ and underweight (ie, WAZ below −2 SD), MUAC and HCZ.

### Explanatory variables

Child’s milk consumption and AFM_1_ levels in milk are the key explanatory variables in this study. Child’s milk consumption will be measured through a 1-day quantitative multiple-pass 24-hour recall interview, consisting of four steps designed to enhance respondent’s recall accuracy.^24^ We will ensure that all days of the week are proportionately represented during the dietary recall, to account for day-of-the-week effects on food intake. We will also collect a second, non-consecutive day 24 hours recall (repeat), within 2–10 days of the first recall, from a randomly selected subsample of children to account for the day-to-day variability of dietary intake within individuals and for nutrients estimation.

At the baseline and the end-line visits, we will collect milk samples (2000 samples in two rounds). AFM_1_ testing in milk, analysis of dilution of milk, nutrients composition and pathogens testing (including *Escherichia coli and Campylobacter* spp) will be conducted at Ethiopian Public Health Institute (EPHI) laboratory following standard operating practices for handling, processing and storing samples.

AFM_1_ in milk samples will be detected by using a commercial ELISA kit (catering to catalogue no. 961AFLM01C-ULTRA), manufactured by Helica Biosystems of Santa Ana, California, USA.^25^ The methodology for conducting the test will be based on the manufacturer’s guidelines. Standards and samples of 200 µl will be replicated in precoated plates. The resulting mixture will be incubated for 2 hours, followed by washing and the addition of conjugates. After the completion of 15 min of additional incubation and subsequent washing, enzyme substrate of 100 µl will be added to each well, permitted to incubate for 15 min and afterwards stopped using 100 µl of stop reaction. Finally, optical density measurements will be taken at 450 nm for each microwell using a microplate reader. Calculation of AFM1 levels achieved by means of a logarithmic standard curve will require an R^2^ value of no less than 95%. The average results from duplicate readings will be used for the presentation of results.^25^

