### Control variables

Data on the control variables will be collected during the survey visits and will include characteristics that are likely to be correlated with child growth outcomes and child’s milk intake. This includes variables such child’s sex, age and diet, parent’s education, household wealth index, milk’s nutrient content, pathogens in milk and child’s maize consumption.

A questionnaire will collect information about child, parent and household characteristics. Information on children’s diet comes from the 24-hour recall survey. We will control for children’s diets by calculating caloric intake variables from eight food groups: (1) Breastmilk, (2) Grains, roots and tubers, (3) Pulses, nuts and seeds, (4) Dairy products, (5) Flesh foods (meats, fish, poultry, organ meats), (6) Eggs, (7) Vitamin-A rich fruits and vegetables and (8) other fruits and vegetables.^26^ Additionally, we will collect detailed data on the non-standard recipe’s ingredients for all mixed dishes that were prepared at home and use standard recipes from the National Food and Nutrition baseline survey dietary data set to assess the amount of food consumed.^27^ The dietary surveys will be administered outside of major Ethiopian Orthodox fasting periods during which dairy household availability and consumption may decline sharply.^28^

One potential source of measurement error in linking food consumption to child growth is within-person variability in consumption. Since linear growth in young children depends on long-term dietary quantity and quality, the 24-hour recall method is imperfect for capturing variability in diets over time.^29^ To address this, we will conduct interim phone surveys every 6 months to ask caregivers about the 24-hour milk consumption and weekly recall of the child’s diet diversity, and assess basic milk production. These higher frequency measurements will be used to assess seasonality, variability, and to adjust for consumption variability in our analysis.

A subsample of 500 livestock feed samples will be collected for testing AFB_1_. Detection of AFB_1_ in feed samples will be achieved using the Helica Low Matrix Aflatoxin B_1_ competitive ELISA kit, manufactured by Helica Biosystems, Santa Ana, California, USA, listed under Catalogue Number 981BAFL01LM-96 and using procedures outlined by them.^30^

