### Data analysis

#### Empirical approach

Descriptive analysis will focus on computing frequencies and percentages for categorical variables and summary statistics (like means, medians SD, IQR) for summarising continuous variables. To determine the association between dairy consumption and growth outcomes in children 6–18 months of age at the baseline, we will specify a least squares regression model as:

(1)
$$Y_{iv}=\alpha +\beta_{M}M_{iv}+X_{iv}^{\prime }\delta +\varepsilon_{iv}$$

where 
$Y_{iv}$
 is the anthropometric outcome for a child *i* residing in enumeration area *v* measured at various time points. Variable 
$M_{iv}$
 measures the child’s milk intake at various time points. The regression controls for child, parent and household characteristics that are captured in vector 
$X_{iv}$
. These control variables are observable characteristics that are likely to be correlated both with a child’s milk intake and his/her growth outcomes. The terms 
α
 and 
$\varepsilon_{iv}$
 in equation (1) represent the intercept and error term, respectively. The coefficient 
$\beta_{M}$
 quantifies the conditional association between a child’s milk intake and subsequent growth outcome, measured either as HAZ at the end line or as change in HAZ between the baseline and end-line surveys. Considering previous evidence from Ethiopia and elsewhere, we expect 
$\beta_{M}$
 >0.

To determine the association between AFM_1_ levels in milk and nutrient density in milk, we will conduct a univariate analysis on each of the macronutrients and micronutrients and then carryout bivariate tests with AFM_1_ levels in the same samples and determine if and how they are associated with each other.

To determine the association between AFM_1_ exposure and growth outcomes in children 6–36 months of age who consume dairy, we will test whether the consumption of AFM_1_-contaminated milk is associated with lower HAZ (ie, more growth faltering) controlling for confounders and co-factors, including the amount of milk consumed and nutrient content and pathogens in the milk. We will append equation (1) with a variable capturing the child’s AFM_1_ exposure (variable 
$A_{iv}$
). In this model, we also control for the estimated macronutrient and micronutrient content and pathogens (vector 
$C_{iv}^{`}$
) in the milk sample collected at the baseline from the household in which the child resides. We will also control for the child’s maize consumption (vector 
$H_{iv}^{`}$

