## Discussion

The results of this study will inform researchers and policymakers on the impact of AFM_1_ in milk on children’s nutrition outcomes and will have implications for the transforming dairy value chains in Ethiopia. Ethiopia has recently adopted strict AFM_1_ standards in milk and other dairy products, which has led to dairy farmers dumping their milk instead of selling it in the market.^12^ An earlier study showed that cancer risk from AFM_1_ consumption was expected to be extremely low.^12^ However, if AFM_1_ has other harmful health effects, such as compromising child growth, then the strict regulations could be justified. In this study, we can determine whether AFM_1_ levels are higher when animals are fed particular feedstuffs, which—if AFM_1_ is correlated with poorer child growth outcomes—will help identify which crops should not be included in dairy feed. But if our work finds that AFM_1_, independently of livestock feed, causes poor child growth outcomes, then the focus need not just be on reducing AFB1 in dairy feed, but also on technologies that can remove AFM_1_ from milk before it is given to children or further processed for other dairy products.

Our work will contribute to rational policymaking and risk communication at local and national levels on whether AFM_1_ poses a risk to children’s health. It will help policymakers and risk communicators in crafting messages balancing the benefits, risks and health outcomes associated with dairy consumption. Secondarily, there could be economic benefits to dairy producers if AFM_1_ is found to have minimal (or no) adverse child growth outcomes, so that standards and regulations can be set at levels appropriate to the true risk, and so that dairy products do not need to be discarded because of overly stringent regulations.^4 39^

There are some limitations of our study. Since a randomised control trial in this context is not feasible, we use a quasi-experimental approach to understand the risks and benefits of child milk consumption in this context and aim to minimise the risk of bias by controlling for observable confounding factors. We use the 24-hour dietary recall and the limitation of this method is that it only captures food intake in the 24 hours prior to the interview. To address this, we will collect data on the consumption of food groups in the past 7 days and also ask whether the milk quantity consumed in the last 24 hours reflects the typical quantity consumed by the child.

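### Balancing recall days over the week makes mean intake representative but does not by itself account for weekday effects in the child-level regressions; recall-weekday indicators would, at almost no cost

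*Protocol article*

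**What the plan says.** In the protocol article, Explanatory variables, a child's milk intake is measured by a "1-day quantitative multiple-pass 24-hour recall interview". Weekday effects are dealt with in one sentence: "all days of the week are proportionately represented during the dietary recall, to account for day-of-the-week effects on food intake". A second recall 2 to 10 days later is taken "from a randomly selected subsample of children to account for the day-to-day variability of dietary intake within individuals"; the size of the subsample is not given.

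Control variables derives the dietary covariates, calories from eight food groups, from the same 24-hour recall. It also acknowledges the wider problem: "One potential source of measurement error in linking food consumption to child growth is within-person variability in consumption". Phone surveys every 6 months repeat the 24-hour milk question and are meant "to adjust for consumption variability in our analysis". The Discussion adds 7-day food-group data and a plan to "ask whether the milk quantity consumed in the last 24 hours reflects the typical quantity consumed by the child".

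Under Empirical approach, milk intake is a child-level regressor in equations (1) and (2), and equation (2) adds maize consumption. Estimation methods specifies ordinary least squares for continuous outcomes. On the covariates, the text says: "The regression controls for child, parent and household characteristics that are captured in vector". The weekday of recall is not named there or in the list of controls, although that list is open-ended.

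**The concern.** Spreading recalls evenly over the week is a sound way to estimate a group mean, because high-milk and low-milk days average out. A regression slope is not computed from the mean. It depends on how each child's recorded value differs from the others, and part of that difference is the day of the week on which the child happened to be recalled. Balance turns the weekday effect into noise spread evenly over children; it does not remove it from any child's value.

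The coefficient concerned is the one on milk, which is the benefit side of the planned benefit-risk comparison. The maize and food-group controls carry the same kind of error. Unlike random day-to-day variation, the weekday part is knowable for every recall, since days cannot be balanced without being tracked. It can therefore be removed at the analysis stage.

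**Working it through.** The article gives no figure for the weekday effect, so there is none to reproduce. The variances below are assumptions, shown over a range.

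**Inputs**
- One recall day per child for most children (Explanatory variables); child-level least squares (Estimation methods).
- n = 900, from 1000 children less 10% attrition (Sample size calculations), taking that loss once.
- Assumed: usual intake has variance 1; vD is the variance due to weekday; vW is the remaining within-child variance. Weekdays are exactly balanced and unrelated to usual intake.

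**Step 1: milk as the only recall-based regressor.** Recorded intake = usual intake + weekday deviation + other error. The fitted slope as a fraction of the true slope is
- balancing only: 1/(1 + vW + vD)
- weekday indicators added: 1/(1 + vW)

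The ratio of the first to the second is 1 − vD/(1 + vW + vD), that is, one minus the weekday share of one-day variance.

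| vW | vD | Balancing only | With indicators | Loss due to weekday |
|---|---|---|---|---|
| 0.5 | 0.02 | 0.658 | 0.667 | 1.3% |
| 0.5 | 0.10 | 0.625 | 0.667 | 6.3% |
| 0.5 | 0.25 | 0.571 | 0.667 | 14.3% |
| 1 | 0.02 | 0.495 | 0.500 | 1.0% |
| 1 | 0.10 | 0.476 | 0.500 | 4.8% |
| 1 | 0.25 | 0.444 | 0.500 | 11.1% |
| 2 | 0.02 | 0.331 | 0.333 | 0.7% |
| 2 | 0.10 | 0.323 | 0.333 | 3.2% |
| 2 | 0.25 | 0.308 | 0.333 | 7.7% |

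A simulation with 900 children and exactly balanced weekdays (400 runs, vW = 1, vD = 0.25) gave 0.445 and 0.500, in agreement with the formulas.

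**Step 2: a second covariate from the same recall.** Let another food have the same variances and a true slope of 0.3, against 0.1 for milk, with usual intakes uncorrelated, vW = 1 and vD = 0.25. Each recorded variable has variance 2.25. Their covariance is +0.25 if both foods rise on the same days and −0.25 if they move oppositely. The milk slope is [2.25 × 0.1 − covariance × 0.3] / (2.25² − 0.25²), and the denominator is 5.
- Same pattern: (0.225 − 0.075)/5 = 0.030, or 0.30 of the truth.
- Opposite pattern: (0.225 + 0.075)/5 = 0.060, or 0.60 of the truth.
- With indicators, either pattern: 0.1/2 = 0.050, or 0.50 of the truth.

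Simulation gave 0.315 and 0.598 without indicators, and 0.517 and 0.496 with them. Omitting weekday can therefore lower or raise the milk coefficient relative to the adjusted fit.

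**Step 3: power, single-regressor case.** Assume a true slope of 0.1 SD per SD of usual intake, reliability 0.5 once weekday is removed, and a two-sided 5% test. Power is approximately Φ(0.1 × √(0.5 × (1 − share)) × √900 − 1.96).
- Weekday removed: Φ(2.121 − 1.96) = 56%.
- Share 2%: Φ(2.100 − 1.96) = 56%. Share 5%: Φ(2.068 − 1.96) = 54%. Share 10%: Φ(2.012 − 1.96) = 52%.

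The gain from removing weekday is about 1, 2 and 4 points. Simulation of similar settings gave gains of 1, 3 and 3 points, with a Monte Carlo standard error of about 1.3 points on each power estimate.

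**The case against.** The strongest reply is that the weekday sentence describes data collection. Balanced days make the intake summaries representative of the week and keep weekday from being confounded with other factors. A set of recall-day indicators is the sort of detail that a condensed article leaves to its analysis plan, and the list of controls is open. That would answer a complaint about a missing covariate. It does not answer this point, because the article names the effect, names the device and says the device accounts for it. For the regressions it goes on to specify, the device falls short.

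A second reply is that the article does not rely on one recall alone. It states that "Since linear growth in young children depends on long-term dietary quantity and quality, the 24-hour recall method is imperfect" and plans repeat recalls, phone recalls and a typical-quantity question. This stands in part. If recalls on different weekdays are combined, or the repeats feed a measurement-error correction, much of the weekday error would be dealt with as well. However, the article does not say how these data enter the equations. The repeat covers only a subsample, and one taken exactly seven days later falls on the same weekday, so the deviation cancels from the difference. The phone rounds give one-day milk intake and diet diversity but no maize or food-group quantities.

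A reader might infer three stronger things. First, that the milk coefficient is necessarily pulled toward zero: this holds only in the single-regressor case, and Step 2 shows it can fail in the planned model. Second, that weekday becomes confounded with locality because teams work area by area: the article does not describe field routing, so this has no basis in it. Third, that the protocol ignores within-child error: it plainly does not.

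**Conclusion.** The point holds as a minor one. Proportional weekday representation secures a representative mean but does not by itself account for weekday effects in equations (1) and (2). With milk as the only recall-based regressor and weekday unrelated to usual intake, the milk slope is reduced by the weekday share of one-day variance, about 1% to 14% over the assumed range. With other covariates from the same recall, the direction is not determined. Nothing in the article shows how strongly milk intake in these children varies by weekday, so the real size is unknown and probably small. Adjustment for weekday leaves the larger attenuation from ordinary day-to-day variation untouched (factors of 0.33 to 0.67 under the same assumptions).

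**What to change.** - Keep the balanced recall days and record the weekday to which each recall refers. The balancing implies this, but the article does not state it.
- Add six recall-weekday indicators to equations (1) and (2). Where several recalls per child are combined, instead centre each recall-derived variable (milk, maize, food-group calories) on its weekday mean before combining.
- Reword the sentence under Explanatory variables so that balancing is said to make mean intake representative of the week, with weekday effects in the regressions handled by the model terms.
- In the same place, state how the repeat and phone recalls enter the equations, since this determines how much weekday error remains.

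The cost is about 6 degrees of freedom out of roughly 900, a line in the model specification and a sentence of text. No new data are needed.
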